### Criteria for Discontinuing or Modifying Allocated Intervention and Comparator

If a participant decides to discontinue the exercise intervention, they will be asked to return for a follow-up visit to complete the week 26 assessments. The reason for discontinuation will be documented. Participants are free to withdraw from participation in the study at any time upon request. An investigator may discontinue a participant from the study, including but not limited to the following reasons: lost to follow-up, unable to contact participant, any event, medical condition, or situation occurs such that continued collection of follow-up study data would not be in the best interest of the participant, or the participant meets an exclusion criterion (either newly developed or not previously recognized) that precludes exercise. In this scenario, the participant would still be followed for outcomes.

If a participant is unable to complete a specific exercise due to injury or discomfort, but still wants to complete the intervention, the Neuro Exercise Specialists will adapt the exercises for that participant while still targeting the intended muscle group as best as possible.

### Strategies to Improve Adherence to Intervention and Comparator

Several measures are taken to improve and monitor adherence. First, participants will be wearing an HR monitor during every endurance exercise session, which will provide them with visual feedback regarding their current HR and exercise duration. The HR monitor will record both the HR and the duration of each exercise session. Participants will be asked to upload the HR monitor data weekly to a secure link so the study team can review and archive it. Second, participants will also be given an exercise diary to record each exercise session. Third, participants will have weekly supervised sessions that will provide accountability and oversight to help with adherence and ensure safe and appropriate use of exercise equipment. Finally, the investigative team will call the participant weekly to review their average HR during exercise, the duration of exercise, and the number of days exercised. If a participant is not adhering to the targets for HR, duration, and frequency, the investigative team and exercise trainers will discuss strategies with the participant to reach appropriate exercise targets.

### Concomitant Care Permitted or Prohibited During the Trial

During this study, any new medications or changes to medication dosage during the study period will be reviewed weekly over the phone. Additionally, participants in the waitlist control group are asked to refrain from increasing their activity level for the duration of the study and keep a physical activity log to track any activities they participate in during the study. Participants are also asked to refrain from enrolling in any other interventional studies.

### Ancillary and Posttrial Care

Given the nature of the intervention, there are no provisions for posttrial care. Participants may keep all home exercise equipment given to them for personal use. Participants in the waitlist control group will be offered the intervention at the conclusion of the study.

### Outcomes

#### Overview

The outcomes for EXCEL-PD are listed below as well as in Table 1, which includes the domain, measure, metric, method of aggregation, and time point for each outcome.

**Table 1. T1:** EXCEL-PD^a^ trial outcomes.

Outcome measure	Domain	Specific measurement variable	Metric	Method of aggregation	Time points
Primary outcomes					
Feasibility	Feasibility	Average % HRmax^b^ and RM^c^	Value at time point assessed	Mean, SD, median, range	Weeks 7‐26
Adherence	Adherence	Number of days exercised per week and duration at target intensity per session	Value at time point assessed	Mean, SD, median, range	Weeks 7‐26
Safety	Safety	Incidence of adverse events and serious adverse events	Number of events	Number and rate of events	Continuous
Secondary outcomes					
Global cognitive function	Cognitive function	Montreal Cognitive Assessment Scale	Score at time point assessed	Mean, SD, median, range	Screening and 26 weeks
MDS-UPDRS^d^ motor score (part III)	Motor sign assessment of Parkinson disease	MDS-UPDRS motor score (part III)	Score at time point assessed	Mean, SD, median, range	Baseline and 26 weeks
Klotho	Neuroendocrine	Klotho protein (nm/L)	Value at time point assessed	Mean, SD, median, range	Baseline and 26 weeks
Cortisol	Neuroendocrine	Cortisol hormone (pg/mL)	Value at time point assessed	Mean, SD, median, range	Baseline and 26 weeks
Brain-derived neurotrophic factor	Neurotrophic	BDNF^e^ protein (pg/mL)	Value at time point assessed	Mean, SD, median, range	Baseline and 26 weeks
C-reactive protein	Inflammation	CRP^f^ protein (mg/L)	Value at time point assessed	Mean, SD, median, range	Baseline and 26 weeks
Exploratory outcomes					
Domain-specific cognitive function	Cognitive function	Trail Making Test, Alternating Verbal Fluency, and NIH^g^ Toolbox	Score at time point assessed	Mean, SD, median, range	Baseline and 26 weeks
Six-minute walk	Functional capacity	Distance walked in 6 minutes in meters	Value at time point assessed	Mean, SD, median, range	Baseline and 26 weeks
VO2peak^h^	Cardiorespiratory fitness	Peak volume of oxygen consumed	Value at time point assessed	Mean, SD, median, range	Baseline and 26 weeks
Hand grip and knee extensor strength	Strength	Maximum strength (kg)	Value at time point assessed	Mean, SD, median, range	Baseline and 26 weeks
Participant-reported outcomes	Quality of life, depression, anxiety, apathy, fatigue, loneliness	The PDQ-39^i^, BDI-II^j^, PAS^k^, AS^l^, PFS-16^m^, UCLA^n^ Loneliness Scale	Score at time point assessed	Mean	Baseline and 26 weeks
Experiences of daily living	Experiences of daily living	MDS-UPDRS part I and II, PDAQ-15^o^	Score at time point assessed	Mean, SD, median, range	Baseline and 26 weeks
Global Impression of Change	Clinical outcome assessment	PGI-C^p^, CGI-C^q^	Score at time point assessed	Mean, SD, median, range	26 weeks

a EXCEL-PD: Exercise for Cognitive Excellence in Parkinson’s Disease.

b HRmax: maximal heart rate.

c RM: repetition maximum.

d MDS-UPDRS: Movement Disorders Society Unified Parkinson’s Disease Rating Scale.

e BDNF: brain-derived neurotrophic factor.

f CRP: C-reactive protein.

g NIH: National Institutes of Health.

h VO2peak: maximum volume of oxygen consumption.

i PDQ-39: Parkinson’s Disease Questionnaire-39.

j BDI-II: Beck Depression Inventory-II.

k PAS: Parkinson Anxiety Scale.

l AS: Apathy Scale.

m PFS-16: Parkinson’s Disease Fatigue Scale.

n UCLA: University of California, Los Angeles.

o PDAQ-15: Parkinson’s Daily Activities Questionnaire-15.

p PGI-C: Patient Global Impression of Change.

q CGI-C: Clinical Global Impression of Change.

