
### Intervention and Comparator

Participants in the exercise group will receive 26 weeks of a home-based, virtually supervised combined endurance and resistance training program. Participants will be provided with required exercise equipment to allow them to exercise at home, including a treadmill, free weights, an exercise bench, and a mat. Exercise equipment will be delivered directly to a participant’s residence for in-home use.

Virtually supervised sessions will be delivered using the Zoom platform (Zoom Video Communications, Inc) by the Movement Revolution, Inc team of Neuro Exercise Specialists (Chicago, IL). All sessions during weeks 1‐2 will be supervised, and they will consist of familiarization sessions led by a Neuro Exercise Specialist who will educate participants on correct and safe use of exercise equipment, including a treadmill and weights. The Neuro Exercise Specialist will review how to get on and off the treadmill safely, how to use handrails on treadmills to assist with balance if needed, and correct form for lifting weights. Participants will also be instructed not to multitask or have distractions around that could increase the risk of falls and never to exercise when feeling lightheaded or dizzy or when Parkinson symptoms are worse than usual. By the end of week 2, trainers will ensure that participants can exercise safely and independently before reducing the number of supervised sessions. If participants or the Neuro Exercise Specialist still have concerns for safety after the initial 2 weeks of training sessions, participants will continue supervised virtual sessions or come to the research center for in-person exercise supervision.

Weeks 3‐6 will include 10 supervised sessions and a ramp-up phase that will include gradual increases in HR for endurance exercise and weights and repetitions for resistance exercises. If a participant is unable to do a particular exercise, the trainer will make modifications as appropriate. By the end of week 6, participants will be exercising 5 days per week (3 days of endurance training and 2 days of resistance training) at their prescribed endurance and resistance intensities. Weeks 7‐26 will be the full intervention and will include 1 supervised session per week.

Endurance training will be performed 3 times per week on a treadmill to target 80%‐85% of their HRmax for a duration of 40 minutes (30 minutes on the treadmill at target HR with 5 minutes each for warm-up and cool-down).

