#### Primary Outcomes

The primary outcomes for the study are feasibility, adherence, and safety of the combined exercise intervention. Adherence and feasibility will only be evaluated in the exercise group. Feasibility will be measured using the average percentage of HRmax for endurance exercise sessions and the average repetition maximum for resistance exercise sessions. Adherence will be measured using the average number of days exercised per week, the duration of exercise for resistance exercise, and the duration of exercise at target HR intensity for endurance exercise. Participants will keep track of exercise sessions using exercise diaries, which investigators will use to assess adherence. Data from Polar HR monitors will be used to assess feasibility. Safety will be measured by the incidence of adverse events (AEs) and serious AEs in the exercise and control groups.

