#### Statistical Methods for Primary and Secondary Outcomes

The primary outcomes are feasibility, adherence, and safety of the combined exercise program. To assess feasibility, we will estimate the overall average %HRmax for endurance training and average repetition maximum for resistance training and their corresponding 95% CIs for the exercise group at 26 weeks. We will then compare the average to the intended target intensity (82.5% for endurance exercise and 10-RM for resistance training) using a 1-sample *t* test (*α*=.05). We will use repeated measures ANOVA of weekly %HRmax and linear mixed models to assess any trends over time from weeks 7 to 26, including a random effect for time within participant as sample size permits. To measure adherence in the exercise group, the average number of days per week exercised and the duration of time (minutes) exercised at the specified intensity will be calculated. Achievement of the adherence (hypothesized to be at least 3 d/wk) will be tested using 1-sided, 1-sample Student independent group *t* tests. To assess safety, the incidence of individual AEs (including serious AEs) and exact CIs will be calculated. We will use Fisher exact or Poisson exact tests to compare exercise and control groups for AEs that are definitely, probably, or possibly related to the exercise intervention as categorical variables.

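### Endurance adherence is measured per session and exercise days are pooled across modalities, so no stated measure shows endurance dose delivered against dose prescribed

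*Protocol article*

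**What the plan says.** Table 1 (Outcomes, Overview) gives the adherence variable as "Number of days exercised per week and duration at target intensity per session", assessed over weeks 7 to 26 and summarised by mean, SD, median and range.

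The Primary Outcomes section lists the components: "Adherence will be measured using the average number of days exercised per week, the duration of exercise for resistance exercise", and endurance time at target heart rate (HR). Days are not split by modality. The section on statistical methods for primary and secondary outcomes says that "the average number of days per week exercised and the duration of time (minutes) exercised at the specified intensity will be calculated". It then sets one criterion, "Achievement of the adherence (hypothesized to be at least 3 d/wk", to be examined with what it calls "1-sided, 1-sample Student independent group" t tests. The null hypothesis is not written out.

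The prescription is under Intervention and Comparator. By the end of week 6 participants should be "exercising 5 days per week (3 days of endurance training and 2 days of resistance training", and each endurance session runs "for a duration of 40 minutes (30 minutes on the treadmill at target HR", with the other 10 minutes for warm-up and cool-down.

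The missing-data section assigns data missing through dropout or noncompliance to multiple imputation. Nowhere does the article say that a session not done counts as 0 minutes, or divide sessions done by sessions prescribed.

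**The concern.** A session that did not take place has no HR recording and no duration. A mean per session therefore leaves it out of both numerator and denominator, unless a rule says otherwise. If the missing-data section were applied to it, it would receive a plausible number of minutes, which is not zero either.

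The days measure does respond to missed sessions. But because it pools the two modalities, a fall from 5 days cannot be attributed to endurance or to resistance, and the criterion of 3 leaves room for two missed days every week.

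Adherence to a combined programme is one of the trial's three primary outcomes, and from week 7 only one session per week is supervised. As written, the plan could declare adherence achieved when much of the endurance dose was not delivered. Readers would then interpret the cognitive, motor and biomarker results against a dose that the reported figures do not describe.

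**Working it through.** **Inputs.** Three endurance and 2 resistance days per week, and a 40-minute endurance session (Intervention and Comparator); weeks 7 to 26 (Table 1); criterion of 3 days per week (statistical methods); 16 in the exercise group (Sample Size).

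**The plan's own figures.** 3 + 2 = 5 days per week. 40 − 5 − 5 = 30 minutes at target. Both reproduce.

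**Prescribed endurance dose.** Weeks 7 to 26 are 26 − 7 + 1 = 20 weeks. 20 × 3 = 60 sessions; 60 × 30 = 1,800 minutes at target; 3 × 30 = 90 minutes per week.

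**Illustrative records.** Assumptions: both resistance sessions done each week, on days separate from endurance, and 30 minutes at target in every endurance session done. With e endurance sessions per week, pooled days = e + 2, minutes per session done = 30, and minutes per prescribed session = 30 × e/3.

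| e | Sessions of 60 | Min per session done | Pooled d/wk | Min/wk (of 90) | Total min (of 1,800) | Min per prescribed session | Share of dose |
|---|---|---|---|---|---|---|---|
| 3 | 60 | 30 | 5 | 90 | 1,800 | 30 | 100% |
| 2 | 40 | 30 | 4 | 60 | 1,200 | 20 | 67% |
| 1.5 | 30 | 30 | 3.5 | 45 | 900 | 15 | 50% |
| 1 | 20 | 30 | 3 | 30 | 600 | 10 | 33% |

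Minutes per session done are the same in every row. Pooled days fall, but no row falls below 3.

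**What pooling hides.** One endurance plus two resistance days gives 1 + 2 = 3 days per week. Two endurance plus one resistance day gives 2 + 1 = 3. Minutes at target per session done are 30 in both, yet the endurance doses are 1/3 = 33% and 2/3 = 67%. If resistance duration is also averaged over sessions done, it does not separate the two records either.

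**Group test.** Assume the null is a mean of at most 3 days per week, one-sided alpha 0.05, n = 16. For a true mean of 3.5 (half the endurance dose), the noncentrality is (3.5 − 3)/SD × √16 = 2/SD. The article gives no SD, so a range is shown, with n = 14 (the per-group number before allowance for attrition) beside it.

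| Assumed SD (d/wk) | Pass probability, n = 16 | n = 14 |
|---|---|---|
| 0.5 | 0.98 | 0.97 |
| 0.75 | 0.82 | 0.76 |
| 1.0 | 0.60 | 0.55 |
| 1.25 | 0.45 | 0.41 |

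For a true mean of exactly 3 (one third of the endurance dose), the pass probability is 0.05, whatever the SD.

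**The case against.** Reporting frequency together with duration per session is a conventional pair, and the frequency half does register missed sessions. A reader might infer that a participant who skips endurance sessions would appear fully adherent on both measures. The documents do not support that: pooled days drop from 5 to 4 or 3, and Table 1's mean, SD, median and range would show it. Only the minutes measure and the 3-day criterion fail to react.

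A reader might also infer that a group skipping two thirds of its endurance sessions would be declared adherent. With full resistance attendance its true mean is exactly 3, and under the null assumed here it would pass only about 5% of the time. The group-level problem concerns means somewhat above 3.

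The exclusion of missed sessions is inferred. Only Table 1 says per session; the Primary Outcomes and statistical methods sections omit the phrase, and no denominator is stated. An article may leave such rules to a fuller document. That does not settle the matter, because the one place that fixes the unit fixes it per session, and the one rule on noncompliance points to imputation.

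The 3-day criterion might be meant for endurance alone, since endurance is prescribed 3 times per week. The one-session participant would then score 1 and fail. No section says so, and the text on days exercised does not separate modalities. The ambiguity is itself something to correct.

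The records above are constructed, with perfect resistance attendance and selective skipping of endurance. They show what the measures cannot distinguish; they do not predict what will happen. Nor does any listed efficacy analysis use adherence, so the consequence there is one of interpretation, not of bias in an estimate.

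**Conclusion.** The point holds in limited form. As defined, the adherence outcome has no component that compares endurance delivered with endurance prescribed. The minutes measure, on the plain reading of Table 1, stays at 30 whether 60, 40 or 20 of the 60 sessions are done. The days measure falls but cannot say which modality was missed, and it is judged against 3 when 5 are prescribed.

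For an individual, 33% of the endurance dose can coincide with the criterion value. For the group, half the endurance dose could be declared adherent with probability of about 0.98 to 0.45. This rests on pooled days, full resistance attendance on separate days, an assumed null of at most 3 days, one-sided alpha of 0.05, and assumed SDs of 0.5 to 1.25. It is a cheap and worthwhile correction to a primary outcome, and does not call the trial's design into question.

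**What to change.** Amend Table 1, the Primary Outcomes section and the statistical methods section as follows, before the analysis planned from June 2026:

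- Report endurance and resistance frequency separately, each as sessions completed over sessions prescribed.
- Derive endurance adherence as total minutes at target HR over weeks 7 to 26 divided by the 60 prescribed sessions, with a session known not to have been done counted as 0. Show it as minutes per week against 90 and as percent of prescribed dose, with a 95% CI.
- Keep minutes per completed session as a descriptive supplement.
- State which frequency the 3-day criterion refers to, and reconcile it with the 5 days under Intervention and Comparator.
- State in the missing-data section that multiple imputation does not apply to sessions known not to have been done.

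The cost is a change of wording and derivation. HR data are already downloaded for each session and diaries record each session, so no new data are needed. The one downside is that the reported adherence figure may be less favourable.

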#### Primary Outcomes

The primary outcomes for the study are feasibility, adherence, and safety of the combined exercise intervention. Adherence and feasibility will only be evaluated in the exercise group. Feasibility will be measured using the average percentage of HRmax for endurance exercise sessions and the average repetition maximum for resistance exercise sessions. Adherence will be measured using the average number of days exercised per week, the duration of exercise for resistance exercise, and the duration of exercise at target HR intensity for endurance exercise. Participants will keep track of exercise sessions using exercise diaries, which investigators will use to assess adherence. Data from Polar HR monitors will be used to assess feasibility. Safety will be measured by the incidence of adverse events (AEs) and serious AEs in the exercise and control groups.

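### The endurance feasibility average is not tied to the 30 minutes of the session that its 82.5% HRmax reference describes

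*Protocol article*

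**What the plan says.** Three parts of the protocol article bear on this point.

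- **The variable.** Primary Outcomes: "Feasibility will be measured using the average percentage of HRmax for endurance exercise sessions". The data come from the Polar monitors, and the section on adherence strategies says these record heart rate and duration for each session. Table 1 sets the window at weeks 7 to 26.
- **The session.** Intervention and Comparator gives endurance training a total of 40 minutes, made up of "30 minutes on the treadmill at target HR with 5 minutes each for warm-up and cool-down".
- **The test.** Statistical Methods for Primary and Secondary Outcomes: "we will estimate the overall average %HRmax for endurance training and average repetition maximum for resistance training", with 95% CIs. The next step is to "compare the average to the intended target intensity (82.5% for endurance exercise and 10-RM for resistance training", "using a 1-sample *t* test (*α*=.05".

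The adherence outcome in the same section is expressly restricted to time at target intensity. The feasibility outcome carries no such restriction, and no statement says that warm-up and cool-down are either included or left out.

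**The concern.** The reference value and the quantity compared with it may cover different minutes. The 82.5% belongs to the 30-minute target phase. The average is described at the level of the session, or of endurance training as a whole, and the article gives both of these a length of 40 minutes. One quarter of that time is expected to be at lower intensity by design.

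This affects a primary outcome with a formal hypothesis test. If the 10 outer minutes enter the mean, a group that delivers the target phase at 82.5% is compared with a value it cannot reach while warm-up and cool-down stay below 82.5%. The trial could then report that the intended intensity was missed when only the averaging caused the gap. The ramp-up is not the cause, because weeks 1 to 6 lie outside the assessment window.

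**Working it through.** **Inputs from the article.** Target zone 80% to 85% HRmax; session of 30 minutes at target plus 5 and 5 minutes; reference 82.5%; 16 participants planned in the exercise group (14 per group before allowance for attrition).

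**Inputs not in the article, assumed.** Mean heart rate in warm-up and cool-down, *w*: 50% to 80% HRmax. For orientation only, ramp-up training starts at 60% HRmax and the treadmill fitness test starts at about 70% of age-predicted HRmax; neither is a stated warm-up value. Between-participant SD of the average: 3 to 10 points. The t test is taken as two-sided, because its sidedness is not stated. The recording is taken to run from the start of warm-up to the end of cool-down.

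**Step 1: the article's own figures.** (80 + 85)/2 = 82.5 and 30 + 5 + 5 = 40. Both reproduce.

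**Step 2: whole-session mean.** With *T* the mean %HRmax in the target phase, session mean = (30*T* + 10*w*)/40.

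For *T* = 82.5:

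| *w* (assumed) | Session mean | Shift from 82.5 |
|---|---|---|
| 50 | (2475 + 500)/40 = 74.4 | -8.1 |
| 60 | (2475 + 600)/40 = 76.9 | -5.6 |
| 70 | (2475 + 700)/40 = 79.4 | -3.1 |
| 75 | (2475 + 750)/40 = 80.6 | -1.9 |
| 80 | (2475 + 800)/40 = 81.9 | -0.6 |

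The half-width of the zone is 2.5 points. The shift exceeds it at *w* = 70 and below, but not at 75 or 80.

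**Step 3: edges of the zone.** The *w* needed for a session mean of 82.5 is (3300 - 30*T*)/10.

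- *T* = 80: *w* = 90.
- *T* = 82.5: *w* = 82.5.
- *T* = 85: *w* = 75. At 85% delivery, *w* = 60 gives 78.75, *w* = 70 gives 81.25, and *w* = 80 gives 83.75, which is above the reference.

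**Step 4: effect on the test.** Probability that the two-sided 1-sample t test (α = 0.05, n = 16, noncentral t) declares a departure from 82.5% when the target phase in truth averages 82.5%:

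| SD (assumed) | *w* = 75 | *w* = 70 | *w* = 60 |
|---|---|---|---|
| 3 | 0.65 | 0.97 | 1.00 |
| 5 | 0.29 | 0.65 | 0.99 |
| 8 | 0.14 | 0.31 | 0.75 |
| 10 | 0.11 | 0.22 | 0.56 |

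With n = 14 and SD 5 the three values are 0.26, 0.58 and 0.97. The nominal rate is 0.05.

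**Step 5: after the fix.** Averaged over the 30-minute phase alone, delivery at 82.5% gives 82.5. The shift is zero and the test keeps its 5% rejection rate.

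**The case against.** The strongest reply is that the article never fixes the averaging window. Speaking of endurance sessions may only separate them from resistance sessions, and a reader who links the target intensity to the 30-minute phase would average that phase. Which minutes of a trace enter a mean is also a processing rule that the full protocol or SAP, neither of which is shown, may contain. This stands in part: whole-session averaging is the most literal reading, not an established fact. But the article does state the variable, its source, the reference, the test and the alpha, and it restricts the neighbouring adherence outcome to time at target while leaving this one unrestricted.

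A second reply is that duration at target intensity is itself a primary outcome and would show good delivery. It would, but it does not correct the separate test against 82.5%.

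A third is that the size is unknown. That is right. With warm-up and cool-down at 75% or more, the shortfall at 82.5% delivery is within the half-width of the zone.

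Two stronger readings are tempting and are not supported. A reader might infer that any in-zone delivery must average below 82.5%; Step 3 shows that 85% delivery with *w* of 75% or more does not. A reader might also infer that in-zone participants would be coached upwards, because staff "call the participant weekly to review their average HR during exercise". The article does not say that this average includes warm-up and cool-down. It gives staying in the zone as the aim of coaching, and it says participants see their current heart rate as they exercise.

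**Conclusion.** The point holds in a conditional form. A primary outcome and its reference value are not tied to the same minutes. If all 40 minutes are averaged, delivery at exactly 82.5% gives about 74.4% to 80.6% for an assumed warm-up and cool-down heart rate of 50% to 75% HRmax, a shortfall of about 2 to 8 points. The direction is certain for delivery at 82.5% with any lower warm-up and cool-down heart rate. The size is not, because the article gives no such heart rate, and the rejection rates in Step 4 also rest on an assumed SD. That the average is wrong by construction does not follow from the article. What follows is that its wording permits a test that rejects under perfect delivery, and that nothing in the text prevents this.

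**What to change.** Before analysis starts, define the endurance feasibility variable as mean %HRmax over the 30-minute main phase, averaged within participant over weeks 7 to 26, and compare that value with 82.5%. Fix the phase by time, for example by dropping the first and last 5 minutes of each recording. Do not fix it by selecting in-zone minutes, which would force the mean into 80% to 85% whatever was delivered. Report the whole-session mean descriptively. If the full protocol or SAP already sets such a window, it is enough to state it with the outcome definition.

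The cost is a change of wording and a trimming step on the downloaded heart-rate files. It requires within-session traces, not only session averages, and a fixed 5-minute cut at each end where phases are not marked. The exercise prescription does not change.
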